### Predictors and moderators of response to internet-based psychotherapy

CBT and IPT are reported to have similar effectiveness in reducing depressive symptoms [44–47]. Donker et al. concluded that, even when treatments are determined equally effective, there are individual characteristics (gender, age, education level, marital status, baseline depression level, coping skills, and previous depression) that influence treatment outcomes [28]. Individual characteristics that influence treatment effectiveness can be broken down into predictors and moderators [28]. Both predictors and moderators are considered pretreatment variables; however, the predictors forecast mental health outcomes in the intervention groups, while moderators identify persons more likely to benefit from particular treatments [28]. Examples of predictors of the efficacy of internet-based interventions include whether the internet-based therapies (CBT, IPT) are guided [28, 48], being female, obtaining low mastery scores on self-mastery measures and low dysfunctional attitudes on coping questionnaires [28]. A moderator of internet-based therapy is age, with evidence indicating that older adults benefit from CBT and younger adults demonstrate larger improvements with IPT [28]. A moderator of IPT is also a role transition, with role transitions occurring in younger adults of childbearing years [28]. Individuals undergoing role transitions are thought to benefit more from internet-based IPT because of the foci of IPT; specifically, interpersonal conflicts and role transitions are particularly relevant in their stage of life [28, 49]. As a result, it is expected that younger adults navigating a significant role transition (e.g., being pregnant and becoming a mother) would benefit from guided, internet-based IPT to improve symptoms of depression, anxiety, stress and interpersonal functioning [50].

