1	To evaluate the clinical effectiveness of online interpersonal psychotherapy versus routine care on reducing stress, anxiety, and depression in prenatal women	What is the effect of an online interpersonal psychotherapy intervention compared to routine care on the percentage of prenatal women with symptoms of stress, anxiety, and depression?	The percentage of prenatal women with stress, anxiety and depression about the clinical cut-offs of validated tools will be significantly lower in the intervention group versus routine care
2	To evaluate the effectiveness of the online interpersonal psychotherapy intervention compared to routine prenatal care on relationship distress	Is relationship distress reduced in the online interpersonal psychotherapy intervention group compared to the routine prenatal care control group?	Relationship distress will be significantly reduced in the online interpersonal psychotherapy group
3	To identify factors, mediators and moderators that are associated with effectiveness of the intervention among participants within the intervention group	What factors, mediators, and moderators are associated with the intervention effect?	Among participants in the intervention group, no factors will be significantly associated with the intervention effect, indicating that online interpersonal psychotherapy is appropriate for prenatal women

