##### Variables

Variables that are associated with (and may mediate) the effectiveness of the e-IPT will be explored through an examination of variables that may be influential in the perinatal mental health theories and literature. The factors to be included were selected based on their association with perinatal depression, anxiety and stress. As a result, the influence of self-efficacy, social support, sense of mastery, self-esteem, sleep, coping, and resilience will be explored. Additionally, the association of preconception of mental health problems such as borderline personality disorder, perfectionism, and attention deficit/hyperactivity disorder will be investigated. These variables will be included as covariates in the data analysis models.

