### Demographic assessment

Demographic information will include marital status, number of children in the home, ethnicity, age, family socioeconomic status (household income, education level) and working status. Assessment of previous mental health problems and assessment of mental health treatment (medication or counseling) will be assessed.

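### Objective 3 seeks moderators of the e-IPT effect, but the list of factors omits age and baseline severity as effect modifiers and enters its variables only as covariates

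*Protocol article*

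**What the plan says.** Objective 3 in Table 2 (Research objectives, questions, and hypotheses) is "To identify factors, mediators and moderators that are associated with effectiveness of the intervention among participants within the intervention group". Its hypothesis is that no factor will be significantly associated with the effect, and it takes that as a sign that e-IPT suits prenatal women.

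The section on predictors and moderators of response to internet-based psychotherapy defines moderators as variables that identify who is more likely to benefit from a given treatment. It states: "A moderator of internet-based therapy is age". It also counts baseline depression level among the individual characteristics that influence treatment outcome, and it ends by expecting benefit in younger adults who are going through a role transition.

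The Variables section then sets out what will be examined. It opens with "Variables that are associated with (and may mediate) the effectiveness of the e-IPT will be explored" and gives the basis of selection: "The factors to be included were selected based on their association with perinatal depression, anxiety and stress". The list follows: "the influence of self-efficacy, social support, sense of mastery, self-esteem, sleep, coping, and resilience will be explored", plus preconception mental health problems. All are to be covariates. The Quantitative analysis section repeats this and keeps only variables that are significant in bivariate analysis. No arm-by-factor term is stated.

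The omitted data are collected. Under Demographic assessment: "Demographic information will include marital status, number of children in the home, ethnicity, age". Under Both groups, the DASS21 and EPDS are completed before randomization.

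**The concern.** The article gives an explicit list and a reason for it, and the list leaves out the one measurable patient characteristic that its own background calls a moderator. It also leaves out baseline severity, which is a natural candidate and is measured before allocation.

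Two things are at stake. First, objective 3 would draw a general conclusion of suitability from null results on a list that never looks at age or severity. Second, the pilot is meant to inform the evaluation strategy of the full trial. If the moderator question is set up as covariate adjustment here, the same structure may carry over to a trial large enough to answer it properly.

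**Working it through.** **1. Rationale against list.**

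| Characteristic | Background | Variables list | Collected |
|---|---|---|---|
| Age | named as moderator | absent | yes, as a demographic |
| Baseline depression level | influences outcome | absent as a modifier | yes, DASS21/EPDS before randomization |
| Coping | influences outcome | present | yes |
| Mastery | predictor of efficacy | present | yes |

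**2. Whether the stated analysis could detect a moderator.** Let the outcome change with factor *x* at slope *b*₀ under routine care and *b*₁ under e-IPT. Moderation is *b*₁ − *b*₀.

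- Covariate entry fits one common slope, so it assumes *b*₁ = *b*₀.
- A look inside the intervention group estimates *b*₁ alone. It cannot separate a factor that predicts outcome in every woman (*b*₁ = *b*₀ ≠ 0) from one that changes the effect.
- Bivariate screening selects on association with the outcome. A factor whose slopes cancel across the arms would be dropped.

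Only an arm-by-factor term in both arms estimates *b*₁ − *b*₀.

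**3. Timing.** Under Both groups, the main T1 questionnaires are completed after randomization. The section on randomization and blinding says women learn their allocation at once. Age cannot be altered by that knowledge, and the DASS21/EPDS screening scores precede it. Both are therefore clean candidates; self-report scales first completed after allocation are less so.

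**4. Precision.** The plan gives no figure for this, so there is none to reproduce. Assume 1:1 arms, a factor that splits women evenly, and a common residual SD of 1. Each of the four cells holds N/4 women, so a cell mean has variance 4/N. The difference of differences has variance 4 × 4/N = 16/N, so SE = 4/√N and the 95% half-width is 1.96 × 4/√N.

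| N | Source | SE (SD) | Half-width (SD) |
|---|---|---|---|
| 160 | pilot sample | 0.316 | 0.62 |
| 112 | 160 × 0.70 | 0.378 | 0.74 |
| 816 | full trial | 0.140 | 0.27 |
| 204 | distressed women in the full trial | 0.280 | 0.55 |

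The 112 assumes that the 25% attrition and 5% loss given under Sample size estimation add up and apply to the pilot. The 204 row applies if the full trial analyses only women with mild to moderate distress.

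For scale, the plan's assumed effect is d = 0.50. At pilot size the half-width of a moderator contrast (0.62) exceeds that whole effect. In 816 women (0.27) it is about half of it.

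**The case against.** Several objections have force.

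- **Role transition.** The background also says "A moderator of IPT is also a role transition, with role transitions occurring in younger adults of childbearing years", so a reader might infer that role transition is a second omitted moderator. The documents do not support that. The background's example of a role transition is pregnancy and becoming a mother, and every participant is pregnant, so in that sense it is constant. First versus later child is a different contrast, which the background does not mention, and number of children in the home is only a proxy for it.
- **Previous depression.** It may look excluded too. But the list says that "the association of preconception of mental health problems such as borderline personality disorder, perfectionism, and attention deficit/hyperactivity disorder will be investigated", which is an open category that can cover it.
- **The listed variables.** A reader might infer from the selection basis that they are merely prognostic. That does not follow: association with distress does not stop a variable from modifying or mediating an effect. Mediation is the role the section names and objective 3 includes. Coping and mastery have support in the background.
- **Age.** The background's evidence contrasts CBT with IPT, and this trial has no CBT arm. An arm-by-age term would not test that contrast. It would address whether the effect against routine care varies with age, which is what objective 3 asks, though only across the ages of pregnant adults.
- **Multiplicity.** Naming moderators does not reduce false signals overall, because the new terms are added to the existing list.
- **Importance and detail.** This is one exploratory objective in a feasibility pilot, and a full moderator list is often left to a fuller document. The first part limits the weight of the point. The second does not remove it, because the article states its list, the reason for it and its analytic use, and these do not fit its own background.

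**Conclusion.** The point holds in limited form. Objective 3 asks about moderators, the background names age and cites baseline depression level, and the stated list and analysis examine neither as an effect modifier, although both are measured. Covariate entry or a within-group look would not answer the question even if the two were added to the list.

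The consequence is modest. At pilot size the interval for an evenly split factor is about ±0.62 SD, or ±0.74 SD with 112 completers, so no moderator could be confirmed or ruled out. The value lies in setting up the correct estimand for the full trial. These widths assume equal arms, an even split and a common residual SD. An uneven split widens them; adjustment for a strongly prognostic baseline narrows them on the raw scale. The conclusion also takes the variables in the Quantitative analysis section to be those under the Variables heading, which is the natural reading.

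**What to change.** - **Variables section:** add age and prerandomization DASS21/EPDS score as prespecified exploratory moderators, estimated as arm-by-factor terms with 95% confidence intervals in all randomised women. First versus later child may be added, with number of children in the home acknowledged as a proxy. The existing list can stay as exploratory.
- **Table 2, objective 3:** replace the restriction to the intervention group, for moderators, with a comparison across both arms, and reword the hypothesis to match.
- **Quantitative analysis section:** exempt the prespecified moderators from bivariate screening, and state that they enter as interactions and not only as covariates. For the severity term, use follow-up scores as the outcome, since the same baseline score should not be both a repeated outcome and the moderator.
- **Reporting:** describe estimates and intervals as descriptive and intended for planning the full trial. Do not read non-significance as evidence that e-IPT suits all prenatal women.

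The cost is short edits in three places and a few model terms on data already held. The downsides are wide intervals and some additional exploratory tests.

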### Demographic assessment

Demographic information will include marital status, number of children in the home, ethnicity, age, family socioeconomic status (household income, education level) and working status. Assessment of previous mental health problems and assessment of mental health treatment (medication or counseling) will be assessed.

### Risks to the safety of participants

#### Intervention group

At the end of each e-IPT module participants will complete question 10 of the EPDS assessing thoughts of self-harm over the last 7 days. A response of anything other than ‘never’ will initiate the study nurse to contact the participant within 24 h.

#### Both groups

Participants who decompensate in their mental health during the course of the study will be able to request mental health support from the study coaches within the online web application. Once this request has been triggered in the system, a study coach will contact the participant within 24 h. If any adverse events occur (increased suicidal ideation, converting from no risk to low or moderate risk) the study nurse has a treatment algorithm in place to triage participants to appropriate acute or long-term treatments, as needed, to ensure the participant’s safety. Additionally, adverse events will be reported to the University of Calgary Ethics Review Board.

### Sample size estimation

The DASS21 categorizes women as having normal, mild, moderate, severe, and extremely severe depression, anxiety and stress [56]. To shift women from ‘midrange’ moderate symptoms down to mild severity on the depression, anxiety and stress subscales, these women would require a reduction of four points in each subscale. Based on the sample size formula for comparison of two means (two-tailed) at a significance level of 5% (1.96), a power of 80% (0.84), and a minimally clinically important difference of four points, 204 women with mild to moderate psychological distress are required in the trial. Based on a 25% prevalence rate of low–moderate prenatal psychological distress [69–71], a final sample size of 816 eligible women (408 per group) would be needed. This corresponds to a moderate effect size (*d* = 0.50) for depression, which is consistent with a meta-analysis of effect sizes of e-IPT [25]. Therefore, this final sample size of 816 participants is adequate to address the primary and secondary research questions of a full trial. Accounting for a participation rate of 50% based on previous studies of psychotherapy in pregnant women [55, 72, 73], the exclusion of 15% of women who do not meet study criteria (5% high psychosocial risk [70, 71, 74], 10% non-English speaking women), an attrition rate of 25% based on previous studies of perinatal IPT [20, 55], and a 5% loss to follow-up, 1592 women would need to be invited to participate in the study to achieve the final full trial sample size. As this is a pilot study, obtaining a sample size of 10% of the full trial sample is sufficient [75]; therefore 160 participants will be included in the pilot study with 80 participants in the intervention and control groups, respectively.

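### The claim that 816 women suffice for every primary and secondary question rests on one two-means calculation, which does not size the factor and moderator question (Table 2, objective 3)

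*Protocol article*

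**What the plan says.** In the protocol article, under Sample size estimation, the method is given as follows: "Based on the sample size formula for comparison of two means (two-tailed) at a significance level of 5% (1.96), a power of 80% (0.84"), with "a minimally clinically important difference of four points". The result is that "204 women with mild to moderate psychological distress are required in the trial". Dividing by a 25% prevalence of distress gives 816 (408 per group). The section adds: "This corresponds to a moderate effect size (*d* = 0.50) for depression". It then concludes: "Therefore, this final sample size of 816 participants is adequate to address the primary and secondary research questions of a full trial".

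The secondary questions are in Table 2, under Research objectives, questions, and hypotheses. The third reads: "What factors, mediators, and moderators are associated with the intervention effect". The matching objective confines the analysis to the intervention group. Its hypothesis is that no factor will prove significant, and that this would indicate the therapy suits prenatal women.

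No other calculation is shown. The document gives no SD, no size for a factor effect and no factor prevalence.

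**The concern.** The adequacy sentence is a positive statement about the design, not a detail left for later. Its shown support covers one contrast: the difference in mean DASS21 between arms among distressed women. The primary questions concern feasibility and acceptability, secondary objective 1 is worded as a percentage, and objective 3 asks whether outcome or effect differs by participant characteristic. A formula for two arm means does not establish adequacy for these.

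Objective 3 is where this has a consequence. For any single factor, a true association that is missed counts in favour of the stated hypothesis. If the sample is described as adequate, a null result will look like evidence of uniform benefit when it may only reflect too few women.

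**Working it through.** **Inputs from the sample size section:** two-sided 5% (1.96), 80% power (0.84), difference 4 points, d = 0.50, 204 distressed women, prevalence 25%, full-trial total 816. Allocation is 1:1 (section on randomization and blinding), so there are 102 distressed women per arm.

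**Inputs the document does not give (assumptions):** a binary factor split 50:50, a four-point difference by factor, and analysis of the distressed women only. All figures use the normal approximation, power = Φ(difference/SE − 1.96).

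**Step 1: the plan's own figure.** Total N = 4 × (1.96 + 0.84)² × (SD/4)².
- With d = 0.50, SD = 4/0.50 = 8 and N = 4 × 7.84 × 4 = 125.4, that is 126 (63 per arm), not 204.
- Solving for N = 204: SD = 4 × √(204/31.36) = 10.2, so d = 4/10.2 = 0.39.
- 204/0.25 = 816 does reproduce.

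The stated effect size and the stated number therefore imply different SDs. Both are carried below as a range.

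**Step 2: the contrast that was sized.** With 102 per arm, power is 80% at SD 10.2 and 94.6% at SD 8.

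**Step 3: objective 3 as worded, within the intervention arm.** The 102 distressed women split 51 v 51. SE = SD × √(1/51 + 1/51) = SD × 0.198.
- SD 10.2: SE = 2.02, 4/2.02 = 1.98, power 51%.
- SD 8: SE = 1.58, 4/1.58 = 2.52, power 71%.

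A two-sample t calculation gives 50% and 71%.

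**Step 4: a moderator as a difference between treatment effects.** The Background describes moderators as identifying who benefits more from a particular treatment, which is a contrast across arms. SE = SD × √(16/204) = SD × 0.280, twice the main-effect SE.
- SD 10.2: SE = 2.86, 4/2.86 = 1.40, power 29%.
- SD 8: SE = 2.24, 4/2.24 = 1.79, power 43%.

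**Step 5: sensitivity.** Each cell gives power at SD 10.2, then at SD 8.

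| Setting | Within arm | Interaction across arms |
|---|---|---|
| Distressed women only, 4 points, 50:50 | 51%, 71% | 29%, 43% |
| Same, factor prevalence 25% | 40%, 59% | 23%, 34% |
| Same, 2 points, 50:50 | 17%, 24% | 10%, 14% |
| All women (408 per arm), 4 points, 50:50 | 98%, >99% | 80%, 95% |
| All women, 2 points, 50:50 | 51%, 71% | 29%, 43% |

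The fourth row requires the four-point effects to hold in all 816 women. If women without distress gained nothing (an assumption), the mean effect over 816 would be 4 × 0.25 = 1 point. Power for a one-point interaction would then be 10% to 14%.

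**The case against.** A reader might infer that power for the moderator question is 29% to 43% with 816 women. The documents do not support that. Those figures are for 204 women analysed, they need a balanced factor and a full four-point interaction, and they test a cross-arm contrast, whereas objective 3 is worded within the intervention group. The eligibility criteria contain no distress threshold, objective 3 is not limited to distressed women, and the analysis is to follow intention to treat. With all 816 analysed and four-point effects throughout, power is 80% or more on either reading. All of this stands, which is why the within-arm figures lead and the assumptions are listed. It does not rescue the adequacy sentence. The four points are derived from moving women out of the moderate range, and the total is inflated because only a quarter are expected to qualify, so nothing in the section supports a four-point effect in everyone.

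It is also fair that the 80% target is attached only to the two-means comparison, and that the Variables section already speaks of exploring these influences. Against that, Table 2 gives objective 3 a testable hypothesis decided by significance.

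A reader might further count the missing effect size for relationship distress (objective 2) as an error. A condensed article may leave that out, and it is not part of this point. Nor is this a flaw in the size of the pilot: the sentence concerns a later full trial, while this study enrols 160 women with feasibility and acceptability as its primary outcome.

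**Conclusion.** The point holds in a limited form. One two-means calculation does not support a claim of adequacy for all primary and secondary questions. For objective 3, power among the distressed women is about 51% to 71% within the intervention arm, and about 29% to 43% for an interaction across arms. Both ranges assume a balanced binary factor and a four-point difference, and their ends reflect the SDs of 10.2 and 8 that the section itself implies. Under the within-arm reading a real four-point difference would be missed about 29% to 49% of the time, and the miss would be read as confirmation. Smaller or unbalanced factors fare worse. The claim could be true for objective 3 only under an effect in all 816 women that the document does not argue for. The practical weight is modest, because no analysis of the pilot depends on the sentence, but the claim could be carried into the planning of the full trial.

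**What to change.** - Restate the sentence so that 816 is described as sized only for the between-arm comparison of mean DASS21 score in mildly to moderately distressed women.
- Label objective 3 exploratory, and report factor and moderator estimates with 95% confidence intervals.
- Reword the hypothesis of objective 3 so that non-significance is not taken as evidence that the therapy is appropriate.
- If a power figure is quoted for objective 3, state the women analysed, the factor split, the difference and the SD, and give the range.
- Because that range depends on the SD, reconcile 204 with d = 0.50 in the same edit.

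The cost is a few sentences in the sample size section and Table 2. No additional participants or data are needed, and the stated reach of the full-trial sample becomes narrower.

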### Inclusion and exclusion criteria

Eligible participants are women who reside in Alberta, Canada, are over the age of 18 years and are pregnant, from conception to 30 weeks gestation. Participants must be able to read and write in English. Participants must be capable of providing informed consent and of learning and understanding new information such as contained in the e-IPT modules. Additionally, participants must have access to online hardware including a digital device (either a computer, smart phone, or tablet).

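### The 1592 invitations cannot yield the 816 women of the full trial at the stated loss rates, and the pilot's 160 is not 10% of 816

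*Protocol article*

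**What the plan says.** All the figures are in the Sample size estimation section of the protocol article.

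- The calculation compares two means at two-sided 5% and 80% power, with a difference of four points, and concludes that "204 women with mild to moderate psychological distress are required in the trial".
- "Based on a 25% prevalence rate of low–moderate prenatal psychological distress", this becomes 816 women, 408 per group. The section calls 816 the final sample size and adequate for a full trial.
- Four losses follow: 50% participation, 15% exclusion (5% high psychosocial risk and 10% non-English speaking), 25% attrition and 5% loss to follow-up. With these, "1592 women would need to be invited to participate in the study to achieve the final full trial sample size".
- The pilot is sized by a fraction: "As this is a pilot study, obtaining a sample size of 10% of the full trial sample is sufficient"; "therefore 160 participants will be included in the pilot study", 80 per group.

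The Inclusion and exclusion criteria section has a counterpart for the language part of the 15% ("Participants must be able to read and write in English"). It lists nothing that corresponds to high psychosocial risk.

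**The concern.** An invitation count that allows for 50% participation must be at least twice the number of women wanted. Twice 816 is 1632, so 1592 is too low before any other loss is applied. The pilot's 160 is about a fifth of 816, although the text presents it as a tenth.

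Two things are at stake. The first is the recruitment plan for the full trial: 1592 understates the effort needed by about 41%. Enrolment and retention are part of this pilot's primary feasibility outcome, so the figure is also a poor benchmark for what the pilot observes. The second is the stated reason for the pilot's size, which does not lead to 160.

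**Working it through.** **Inputs (all from Sample size estimation).** 204 distressed women; prevalence 25%; participation 50%; exclusion 15% (5% + 10%); attrition 25%; loss to follow-up 5%; invitations 1592; pilot fraction 10%; pilot size 160.

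**1. The plan's own figures.**
- 204 / 0.25 = 816, as stated.
- 816 × (1 + 0.50 + 0.15 + 0.25 + 0.05) = 816 × 1.95 = 1591.2, rounded up to 1592, as stated. The article shows no formula, so this additive route is inferred. Of the formulas tried that use all four losses, it is the only one that reproduces the figure. Successive mark-ups, 816 × 1.50 × 1.15 × 1.25 × 1.05, give 1848.

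**2. What 1592 invitations yield at the stated rates.**
- After participation: 1592 × 0.50 = 796
- After exclusion: 796 × 0.85 = 677
- After attrition and loss to follow-up: 1592 × 0.50 × 0.85 × 0.75 × 0.95 = 1592 × 0.3028 = 482, which is 59% of 816

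**3. Invitations needed for 816: 816 divided by the product of the retained fractions.**

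| Reading of the losses | Formula | Invitations (about) |
|---|---|---|
| All four, compounded | 816 / (0.50 × 0.85 × 0.75 × 0.95) | 2695 |
| 5% high-risk exclusion dropped | 816 / (0.50 × 0.90 × 0.75 × 0.95) | 2545 |
| 5% loss already inside the 25% attrition | 816 / (0.50 × 0.85 × 0.75) | 2560 |
| Attrition and loss pooled at 30% | 816 / (0.50 × 0.85 × 0.70) | 2743 |
| Participation and exclusion only | 816 / (0.50 × 0.85) | 1920 |
| Participation only | 816 / 0.50 | 1632 |

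Even the last two rows, which leave out losses that the section says it allows for, exceed 1592. Against 2695, the shortfall is 1 − 1592/2695 = 41%.

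**4. The pilot's 10%.**
- 0.10 × 816 = 81.6, so 82 women (41 per group)
- 160 / 816 = 19.6%
- 0.10 × 1592 = 159.2, which rounds up to 160

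**5. What 160 does deliver.**
- Invitations for 160 enrolled: 160 / (0.50 × 0.85) = 377, or 160 / (0.50 × 0.90) = 356 without the high-risk exclusion.
- Precision of a retention proportion in 80 e-IPT women: at 75%, 1.96 × √(0.75 × 0.25 / 80) = ±9.5 points; at 0.75 × 0.95 = 71%, 1.96 × √(0.71 × 0.29 / 80) = ±9.9 points.

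**6. Power if a full trial really stopped at 1592 invitations.** 482 × 0.25 = 121 distressed women, about 60 per arm. The section states d = 0.50, but 102 per arm at 80% power implies d = (1.96 + 0.84) / √(102/2) = 0.39. Power is approximately Φ(d × √(60/2) − 1.96):
- d = 0.39: about 57%
- d = 0.50: about 78%

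**The case against.** The best defence is that 1592 governs nothing in this pilot. No randomisation, outcome or analysis uses it, and the abstract's Discussion says the pilot will inform the sample size calculations for the full trial, so these rates would be re-estimated first. That stands, and it limits the severity.

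A reader might infer that the full trial would lose power, from 80% to 57%. The article does not support this. The target is 816 and nothing caps invitations at 1592, so the likelier result is longer recruitment. The 57% also rests on a back-calculated d = 0.39; at the stated d = 0.50 the figure is about 78%.

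A reader might also infer that the pilot is too small. It is not: 160 is nearly twice the 82 that the rule gives.

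The origin of both numbers is inferred. The additive match for 1592 is exact but not documented. For 160, 10% of the invitations fits best, but a slip between total and per-arm size is possible, since 81.6 is close to 80 per group.

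Finally, 2695 is only as good as 816. At d = 0.50 the usual formula needs 126 distressed women, not 204. That would give 126 / 0.25 = 504 women and 504 / 0.3028 = 1664 invitations. This is a separate inconsistency, and it is a reason to present 2695 as conditional.

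None of this rescues the text as written. From 816 and the stated rates, 1592 fails on participation alone, and 160 is not 10% of 816.

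**Conclusion.** Both statements are wrong as written. At the stated rates 1592 invitations yield about 482 women rather than 816. The matching invitation figure is about 2695, given 816 and the 15% exclusion, with a range of about 2545 to 2743 over the readings that keep both attrition and participation. The pilot's 160 is 19.6% of the full trial sample, not 10%.

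The 5% high-psychosocial-risk exclusion inside the 15% has no counterpart in the eligibility criteria. The Intervention section moreover has coaches contacting participants with very high symptoms or complex needs, so it expects such women in the trial. These sections must be reconciled; the article does not settle which is intended.

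Severity is moderate. The full-trial recruitment plan and the justification of the pilot size are affected; the adequacy of the pilot is not.

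**What to change.** In Sample size estimation:

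1. Replace 1592 with a figure from the product formula and print the formula: about 2695 if 816 and the 15% exclusion both stand. Say whether the 5% loss to follow-up is additional to the 25% attrition, part of it (2560), or pooled with it at 30% (2743).
2. Reconcile the 5% high-psychosocial-risk exclusion with the Inclusion and exclusion criteria section. If it is dropped from the calculation, the figure becomes about 2545.
3. Keep 160 but delete the statement that it is 10% of the full trial sample. State what 160 provides: for example, 80 e-IPT women give a 95% confidence interval of about ±9.5 to 10 points around 71–75% retention. Add that enrolling 160 takes about 356 to 377 invitations at the stated rates.

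The cost is a text correction. No pilot participants are added and no analysis changes; the stated full-trial invitation figure becomes less favourable.
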